## Abstract

**Introduction:**

*In vitro* fertilization (IVF) is a technology that assists couples experiencing infertility to conceive children. However, unsuccessful attempts can lead to significant physical and financial strain. Some individuals opt for electro-acupuncture (EA) during IVF, even though there is limited evidence regarding the efficacy of this practice. Thus, this pilot study aims to explore the effectiveness and safety of EA during IVF on pregnancy outcomes.

**Methods and analysis:**

This clinical trial is a parallel, randomized, sham-controlled study. It aims to include a total of 118 infertile women who intend to undergo IVF. The participants will be randomly divided into three groups in a 1:1:1 ratio: the EA + IVF group, the placebo electro-acupuncture (pEA) +IVF group, and the IVF control group. All of the patients will be required to use ovarian stimulation drugs, while those in the EA + IVF and pEA + IVF groups will receive acupuncture treatment at three sessions per week (every other day) until trigger day with a minimum five session. The primary outcome of this trial will focus on the clinical pregnancy rate (CPR). CPR is defined as the rate of achieving clinical pregnancy from the first fresh/frozen embryo transfer cycle with an ultrasound-confirmed gestational sac in the uterine cavity. The secondary outcomes will assess embryology data, biochemical pregnancy rate, early miscarriage rate, Self-rating Anxiety Scale (SAS), Self-rating Depression Scale (SDS), Pittsburgh Sleep Quality Index (PSQI), Fertile Quality of Life (FertiQoL), patient retention rate, treatment adherence, and safety outcomes.

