#### Secondary outcomes

The secondary outcomes include embryology data, other pregnancy outcomes, and the scale and questionnaire measurement. The schedule of measurements and visits for each outcome are shown in **Table 4**. We will also observe the patient retention rate and treatment adherence. Retention rate is defined as the percentage of patients enrolled at baseline and who completed all follow-up measurements. Treatment adherence is assessed using attendance at the treatment sessions. Successful pilot targets are defined as the recruitment of 114 participants over 4 months, an 80% retention rate (25), and at least four treatment sessions attended.

Embryology data include total ova retrieved and total high-quality embryos. The high-quality embryos will be graded according to the guidelines (26, 27) by embryologists. Cleavage-stage embryos and blastocyst-stage embryos will be recorded separately.

The follow-up of pregnancy outcomes will be observed around 14 days and 12 weeks after embryo transfer. Besides CPR, the biochemical pregnancy rate (BPR), embryo implantation rate, and early miscarriage rate will also be observed, respectively. BPR is defined as the level of human chorionic gonadotropin (hCG) >5 mIU/mL (28). The fertilization rate is defined as the number of 2PN embryos divided by the number of inseminated oocytes. The early miscarriage rate is defined as the fetal growth stops or the absence of heart activity in the gestational sac within the first 12 weeks of pregnancy.

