### Sample size

The purpose of this study was to evaluate the study’s feasibility and support the development of a future definitive RCT. Utilizing the upper confidence limit method, we determined that a pilot sample size of between 20 to 40 individuals can serve as a benchmark (34). Based on the consensus of the methodologists, statisticians, and acupuncturists, we decided that a sample size of 30 in each group (25) and a 20% estimated dropout rate were sufficient; thus, the total of 114 patients would be considerable (38 in each group).

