
There are certain limitations to consider. Firstly, due to the inherent nature of acupuncture, it is impractical to blind either the acupuncturists or the patients during the treatment process when comparing the EA + IVF group with the IVF control group. Secondly, our study was confined to a single-center trial involving 118 patients, potentially introducing selection bias. Nevertheless, for future trials, we aim to recruit patients from multiple centers in a significantly larger sample size to mitigate these limitations.

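### Planned enrolment is given as 118 in the abstract and limitations but as 114 in the sample-size section and the recruitment target; only 114 follows from the stated inputs

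*Protocol article*

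**What the plan says.** The total appears in four places in the protocol article.

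- Abstract, Methods and analysis: "It aims to include a total of 118 infertile women who intend to undergo IVF".
- Discussion, limitations paragraph: "our study was confined to a single-center trial involving 118 patients".
- Sample size: "we decided that a sample size of 30 in each group (25) and a 20% estimated dropout rate were sufficient", which leads to "thus, the total of 114 patients would be considerable (38 in each group".
- Secondary outcomes, pilot targets: "Successful pilot targets are defined as the recruitment of 114 participants over 4 months, an 80% retention rate".

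Two further statements bear on the point. The abstract and the section on randomization and allocation concealment both specify 1:1:1 allocation to three groups, and the latter adds stratified blocks of 3 or 6. The Trial status section says that recruitment is still open, so 118 cannot be read as a final count of women enrolled.

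**The concern.** Both figures are plans for the same quantity, so they cannot both be right. Each appears twice, in running prose and in separate sections, which makes a single typing slip an unlikely explanation. Nothing in the article marks either figure as superseded.

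What is at stake is the record of what was planned. Recruitment is one of the feasibility aims of this pilot, and the final enrolment will be compared with the plan. A reader who starts from the abstract would call 114 women a shortfall of four. A reader who starts from the Sample size section would call the same result full attainment, and would call 118 an overrun of four.

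**Working it through.** **Inputs.** Evaluable women per group: 30 (Sample size). Dropout: 20% (Sample size). Groups: 3, allocated 1:1:1 (abstract; Randomization and allocation concealment). Stated totals: 114 (Sample size; Secondary outcomes) and 118 (abstract; Discussion).

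**Step 1: reproduce 114.** Per group, n/(1 − d) = 30/(1 − 0.20) = 37.5, rounded up to 38. The total is 3 × 38 = 114. The article's own figure reproduces exactly.

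**Step 2: try to reach 118 from the same inputs.**

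| Method | Calculation | Total |
|---|---|---|
| Inflate each group, round up | 3 × 38 | 114 |
| Inflate the pooled total, round up | 90/0.8 = 112.5 | 113 |
| Multiply by 1 + d | 3 × 30 × 1.2 | 108 |

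None of these gives 118.

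**Step 3: what would be needed to reach 118.** Starting from 90 evaluable women, the dropout rate would have to be 1 − 90/118 = 23.7%, or 118/90 − 1 = 31.1% if the inflation is done by multiplying. The article states neither rate. Changing the group size at 20% dropout does not help either. The section also says "we determined that a pilot sample size of between 20 to 40 individuals can serve as a benchmark", so every whole number from 20 to 40 per group was tried with the three methods, and none gives 118. The nearest results with inflation of each group are 117 (31 per group) and 120 (32 per group).

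**Step 4: fit with the allocation.** 114/3 = 38 exactly, which agrees with the stated group size. 118/3 = 39.33, remainder 1, which agrees with neither 38 per group nor any other equal split.

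**Step 5: size of the discrepancy.** 118 − 114 = 4 women; 4/114 = 3.5%. After 20% dropout, 114 leaves 91.2 evaluable (30.4 per group) and 118 leaves 94.4 (31.5 per group). Both reach the intended 30 per group. Standard errors scale with 1/√n, so their ratio is √(118/114) = 1.017, a difference of about 1.7%.

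**The case against.** The strongest reply is that little depends on the difference. The two places that govern conduct, the Sample size section and the pilot target, agree with each other. The outlying figure sits in the abstract and in one sentence on limitations. The sample size rests on a pilot benchmark and a consensus choice, not on a power calculation, and the Statistical analysis section calls the results exploratory. All of this stands, and it limits the seriousness of the point.

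Three stronger readings are tempting, and the article does not support them.

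- *A reader might infer that the recruitment success criterion is ambiguous.* It is not. It is stated once, as "the recruitment of 114 participants over 4 months", and 118 is never offered as a success target. Enrolling 118 within that period would also meet it.
- *A reader might infer that 118 would damage the balance between arms.* Stratified blocks of 3 or 6 can end incomplete in any stratum, so 38/38/38 is not guaranteed at 114 either, and a 40/39/39 split does no harm. The divisibility argument shows only that 118 is an odd choice for a planned total under 1:1:1 allocation and conflicts with 38 per group.
- *A reader might infer that two totals allow a selective choice of when to stop.* The article describes no interim look, and it says that the analyst and the physicians collecting outcome data are blinded. It shows no route by which a margin of four women could be exploited.

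It can also be said that changing 118 to 114 presumes which figure was intended. That is fair. 114 is much the better supported, but the randomisation list and the registry record are not available here and should be consulted before the text is changed.

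None of this removes the contradiction. A fuller protocol could show which total is right, but it could not make both right.

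**Conclusion.** The point holds as a minor wrong figure. The article states two planned totals that differ by 4 women, and only 114 can be obtained from its own inputs. The arithmetic in the Sample size section is correct; the fault is that the abstract and the limitations paragraph disagree with it. The effect on precision is negligible, and the design, the analysis and the success criterion are unaffected.

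The conclusion assumes that the stated 30 per group and 20% dropout are the inputs actually used. It also assumes that 118 is a planned number, which the abstract's wording and the open recruitment both indicate.

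**What to change.** Check the total on the randomisation list and in the trial registration. If they show 114, restate 118 as 114 in the Methods and analysis part of the abstract and in the limitations paragraph of the Discussion. If 118 is the intended total, give its derivation, then revise the group size in the Sample size section and the recruitment target under Secondary outcomes so that all four places agree.

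The cost is two wording corrections and one check against existing records. If 118 is kept, it is a short derivation and two changed figures. Nothing in the conduct or analysis of the trial needs to change if 114 is confirmed.

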**Ethics and dissemination:**

Ethics approval was obtained from the Ethics Committee of Sichuan Jinxin Xi’nan Women and Children Hospital (number 2021–007). The results will be disseminated through peer-reviewed publications. The participants gave informed consent to participate in the study before taking part in it.

**Clinical trial registration:**

https://www.chictr.org.cn, identifier ChiCTR2300074455.

## Highlights

This study is the first to provide information about the effectiveness and safety of electro-acupuncture (EA) treatment for infertile women undergoing *in vitro* fertilization (IVF). The study compares EA *versus* placebo EA and a control group.The study will use a rigorous methodology to reduce the risk of bias, including adequate randomization, quality control, and blinded outcome assessors and statisticians. Eligible participants will be strictly recruited and screened, and a standard operating procedure will be conducted rigorously to ensure quality control.Due to the nature of acupuncture, only EA and pEA group participants can be blinded. Treatment providers are likely to bring bias and influence the results.

## Introduction

Infertility is a global health issue affecting millions of people of reproductive age worldwide; it is defined as the failure to achieve a successful pregnancy after ≥12 months of regular, unprotected sexual intercourse (1). People with infertility are estimated to be at 48 to 186 million worldwide (2). Approximately 2.0% of all infants born in the United States each year are conceived by assisted reproductive technology (ART) (3). Despite technological advances, the average live birth rate by *in vitro* fertilization (IVF) remains low, with only 23%–26.9% per embryo transferred (4–6). The financial burden of repeated IVF cycles can be substantial, placing a significant economic pressure on affected patients and their families. Therefore, ensuring that the procedure’s efficiency is maximized while providing effective and safe strategies to assist infertile couples is imperative.

Patients have turned to complementary and alternative medical (CAM) treatments to increase the success rate of IVF. Among these CAM treatments, acupuncture is a frequently used adjunctive therapy (7). Since the first RCT reported by Paulus (8) in 2002 suggesting that acupuncture can increase the clinical pregnancy rate (CPR) of IVF, the application of acupuncture to IVF has attracted great interest from the international community. However, previous randomized clinical trials (RCT) (9–11) prevented a thorough evaluation of the beneficial effects of acupuncture in improving pregnancy outcomes with statistical heterogeneity (10); therefore, the efficacy is still controversial and remains debatable.

Acupuncture has a dose–effect relationship. Although patients may benefit from two acupuncture treatment sessions (8), many studies (12–14) failed to repeat this outcome. In our previous meta-analysis (15), a clear dose–response relationship with the pregnancy outcomes was revealed. Another study (16) suggested that patients receiving acupuncture before the stimulation of IVF, at two sessions per week for more than 4 weeks, may benefit more than those patients treated just pre-/post-ET. Based on previous clinical experience, we speculate that three sessions per week until the human chorionic gonadotropin (hCG) trigger day may be an effective therapy for women undergoing IVF.

Therefore, we have proposed to conduct a prospective, parallel, randomized, placebo-controlled trial that will be carried out to investigate the efficacy and safety of acupuncture treatment for patients with infertility, comparing them with placebo electro-acupuncture and IVF control groups. The current pilot study aims to assess the feasibility of performing a large-scale RCT, including patient recruitment, retention, and treatment adherence.

## Methods and design

### Study design

This randomized, sham-controlled, prospective randomized trial will be conducted at the reproductive center of ichuan Jinxin Xi’nan Women and Children Hospital. The protocol has received approval from the Ethics Committee of Sichuan Jinxin Xi’nan Women and Children Hospital (number 2021–007) and has been registered at ClinicalTrials.gov (ChiCTR2300074455). The protocol will report with the Standard Protocol Items: Recommendations for Interventional Trials (SPIRIT) guidelines (17) and Standards for Reporting Interventions in Controlled Trials of Acupuncture (STRICTA) (18). The placebo acupuncture will be reported with Sham Acupuncture Reporting (SHARE) guidelines (19). **Figure 1** displays a flow chart of the trial. In addition, the schedule of enrollment, interventions, and assessments during the study period is shown in **Table 1**.

**Figure 1 f1:**
[figure not shown]
Flow diagram. IVF, *in vitro* fertilization; EA, electro-acupuncture.

**Table 1 T1:** Schedule of recruitment, intervention, and measures.

Items	Enrolment	Intervention	Follow-up			
	Screening and baseline assessment	Controlled ovarian hyperstimulation	Oocyte retrieval	Embryo transfer	14 days after embryo transfer	28 days after embryo transfer
Enrolment						
Eligibility screen	×					
Informed consent	×					
Allocation	×					
Baseline data	×					
Randomization						
Randomization	×					
Allocation	×					
Interventions						
EA/ pEA treatment		×				
COH treatment		×				
Assessments						
Laboratory tests	×	×	×	×	×	×
Embryo quality				×		
Pregnancy tests					×	×
Pregnancy outcomes				×	×	×
Fetus information						
FertiQoL	×		×			
SAS	×		×			
SDS	×		×			
PSQI	×		×			
Blinding assessments			×			
Adverse events		×	×	×	×	×
Retention rate						×
Adherence to treatment						×

EA, electro-acupuncture; pEA, placebo electro-acupuncture; COH, controlled ovarian hyperstimulation; FertiQoL, fertile quality of life; SAS, self-rating anxiety scale; SDS, self-rating depression scale. PSQI, Pittsburgh Sleep Quality Index.

### Recruitment of participants

Women diagnosed with infertility and undergoing IVF will be recruited through advertisements on the official accounts of Sichuan Jinxin Xi’nan Women and Children Hospital and through posters and WeChat. The clinical doctors of the reproductive centers will make the diagnoses based on the chief complaints, present illness, and physical examinations (1). The patients will be well-informed and write the consent before randomization.

#### Inclusion criteria

Women who are diagnosed with infertility (1) and will undergo IVF or Intracytoplasmic sperm injection (ICSI) who have met the following criteria will be recruited: (1) ages between 21 to 42 years old, (2) with GnRH-a or GnRH-A ovarian stimulation protocol, (3) AMH >1.2 ng/mL (20), (4) previous IVF/ICSI cycle ≤2, and (5) written informed consent.

#### Exclusion criteria

Patients will be excluded due to (1) preimplantation genetic testing (PGT), (2) malformation of the uterus: unicornuate uterus, bicornuate uterus, bicornuate uterus, or untreated uterine septum, (3) damage to the endometrial cavity or not cured diseases, such as submucosal myoma and uterine adenomyosis uterine adhesions or scar uterus, (4) diagnosed with an endocrine disorder: untreated hyperprolactinemia, hypothyroidism, hyperthyroidism, hyperandrogenism, chronic adrenocortical, and hypofunction, (5) diagnosed with polycystic ovary syndrome (PCOS), (6) having received acupuncture for infertility within the past 3 months, and (7) with bleeding tendency and infection, or severe allergies, or skin ulcers; scars are prohibited from acupuncture.

### Randomization and allocation concealment

Randomization will be conducted after the patients agree to consent to undertaking acupuncture treatments. Patients will be randomized according to the randomized number table generated by SPSS (version 27.0, IBM, Armonk, NY, USA) after completing the baseline assessments. Patients will be randomized into three groups: electro-acupuncture with IVF treatment (EA+ IVF group), placebo electro-acupuncture with IVF treatment (pEA + IVF group), and only IVF control (IVF group) in a 1:1:1 ratio using stratified block randomization (block = 3 or 6, randomly). An independent statistician with no clinical role in this study will comply with the randomization sequence. Allocation concealment was ensured by using a telephone by an independent third party to ensure objectivity and minimize the risk of bias.

### Blinding

Owing to the characteristics of the acupuncture procedure, the acupuncturists involved will not be blinded. In the EA + IVF group and pEA + IVF group, the single-blind will be conducted. The atmosphere of treatment, the communication between the acupuncturists and the patients, and the superficial appearance of the acupuncture techniques were the same. The apparatuses of the two groups are the same and can work normally. The study participants, fertility specialists, nurses, and the analyst were blinded to group allocation. The acupuncturists were not blinded to group allocation. Study site research physicians who were blinded to group allocation enrolled women in the study and collected clinical outcome data. Blinding was maintained until the completion of the analysis.

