### Intervention

Patients in the three groups will receive GnRH-a or GnRH-A protocol according to the previous study (21, 22). Egg retrieval, fertilization, and embryo transfer were determined by their fertility specialists. During the study period, the patients’ medications, including dose and types, should be recorded in detail.

Following the randomization, the patients who were randomized into the EA + IVF group and the pEA + IVF group will receive EA treatment during the ovarian stimulation phase at three times per week (every other day) until trigger day with a minimum five session. Each session will continue for 30 min. Licensed acupuncturists possessing a minimum of 1 to 3 years of clinical experience will undergo training in a standardized operating procedure. This training aims to impart a comprehensive understanding of the precise locations of acupoints and non-acupoints. Additionally, they will acquire proficiency in needle manipulation and the operation of electro-devices. Only acupuncturists who have completed this training will be authorized to perform acupuncture treatments.

The disposable needles (Hwato, Suzhou, Jiangsu, China) and the SDZ-V EA apparatus (Suzhou Medical Appliance) have the same appearance. The needle device used for blinding is comprised of a sticky plastic plate with a guide tube. The needles and blunt-tip needles will be administered through the guide tube and the hole of the plastic plate.

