### Statistical analysis

Intention-to-treat (ITT) analysis encompassing all randomized patients will be conducted for all efficacy analyses. Additionally, a per-protocol (PP) analysis focusing on the primary outcome will be performed as a sensitive analysis, excluding patients who did not complete the acupuncture treatment. Missing outcome data will be complemented using multiple imputations with the package “Mice” from the R software (www.r-project.org).

Categorical variables will be reported by number and percentage, whereas continuous variables will be represented by mean and standard deviation (SD) (or median and interquartile range, IQR). The retention rate and treatment adherence will be reported in descriptive statistics.

For the primary outcome, CPR will be compared by the proportions of included patients with clinical pregnancy. To determine the independent factors, logistic regression will be used to identify baseline variables that are associated with outcomes. The retention rate and rates of biochemical pregnancy, ongoing pregnancy, blinding assessments, and adverse events will undergo statistical analysis using chi-squared tests or Fisher’s exact test. Other outcomes will be evaluated using one-way variance (ANOVA) models or Kruskal–Wallis analysis. The score of SAS, SDS, FertiQol, and PSQI, respectively, will be assessed at baseline and after treatment among groups on hCG trigger day. Statistical significance will be determined at *P <*0.05. Pairwise comparisons will be performed between the EA + IVF group and the pEA + IVF group and between the EA + IVF group and the IVF group in a *post hoc* analysis.

A predetermined subgroup analysis will be performed to determine whether the baseline characteristics (female age, ovarian stimulation protocol, etc.) affect the CPR to EA. The data was analyzed using SPSS version 27.0 (IBM, Armonk, NY, USA). As this is a pilot study, our results were considered exploratory.

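### Participant blinding is stated without naming arms, although women in the IVF arm cannot be blinded, and the self-rated scales are tested across all three arms with EA versus pEA left to a post hoc contrast

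*Protocol article*

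**What the plan says.** All references are to the protocol article.

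- **Blinding.** The section first limits the blind: "In the EA + IVF group and pEA + IVF group, the single-blind will be conducted". A few sentences later it says, with no arm named, "The study participants, fertility specialists, nurses, and the analyst were blinded to group allocation", and adds that blinding was kept until the analysis was finished.
- **Discussion.** The paragraph on design strengths lists blinding of patients among the demands the trial meets, again without naming arms. The limitations paragraph says that, for EA + IVF against the IVF control, "it is impractical to blind either the acupuncturists or the patients during the treatment process".
- **Highlights.** "Due to the nature of acupuncture, only EA and pEA group participants can be blinded".
- **IVF control group.** These women have no EA treatment during ovarian stimulation.
- **Blinding assessment.** Only EA and pEA patients are asked to guess what they received.
- **Scale and questionnaire measurement.** SAS, SDS, PSQI and FertiQoL are patient questionnaires, taken at baseline and on trigger day.
- **Statistical analysis.** The four scales are assessed among groups on trigger day. "Other outcomes will be evaluated using one-way variance (ANOVA) models", with Kruskal–Wallis as the alternative. EA versus pEA and EA versus IVF follow as post hoc pairwise comparisons. The significance level is 0.05, and the results are described as exploratory.

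**The concern.** A reader judging risk of bias goes to the Methods, and there finds a sentence that gives all participants a blind that one arm cannot have. The same article states the limit elsewhere, so the fault is inconsistent wording rather than concealment. The limit is not carried into the analysis of the outcomes most exposed to it.

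Self-rated anxiety, depression, sleep and quality of life respond to expectation and attention. Both acupuncture arms receive 30-minute sessions three times a week, and the IVF arm receives none. Women are randomised after agreeing to undertake acupuncture, so controls know that they did not get it. A three-group test on these scales combines two arms that are blinded to each other with one open arm. The contrast that removes the difference in expectation and attention, EA versus pEA, is only post hoc. The contrast that would show that difference directly, pEA versus IVF, is not planned.

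At stake is the interpretation. A significant overall result, or a significant EA-versus-IVF result, could be read under a stated participant blind as an effect of EA when it shows nothing beyond sham. The pilot is meant to inform a definitive trial, so the misreading could carry forward.

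**Working it through.** **Step 1: compare the statements, by arm.**

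| Place | EA and pEA women | IVF women |
|---|---|---|
| Blinding, earlier sentence | single-blind | not named |
| Blinding, later sentence | blinded | blinded, by lack of qualification |
| Discussion, design strengths | blinded | blinded, by lack of qualification |
| Highlights | can be blinded | cannot be blinded |
| Discussion, limitations | not addressed for EA versus pEA | patients not blindable for EA versus IVF |
| IVF control group | not applicable | no sessions, so allocation is known |

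Two statements are unqualified. The other four limit the blind, or show why it cannot extend to the IVF arm.

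**Step 2: share of women affected.** The Sample size section gives 30 per group and 20% dropout: 30 / (1 − 0.20) = 37.5, rounded up to 38, and 3 × 38 = 114. The plan's figure reproduces. The open arm is 38 / 114 = one third. (The Abstract and the limitations paragraph give 118; the 38 per arm used here comes from the Sample size section.)

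**Step 3: how often a shift in the open arm alone gives a significant three-group test.**

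Inputs from the article: three groups, 38 per arm randomised or 30 after dropout, alpha 0.05. Assumptions: EA = pEA exactly; the IVF arm differs from both by b SD through expectation and attention; SD 1 in each arm; one-way ANOVA. The article gives no size for b, so a range is shown.

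With means (b, b, 0) the grand mean is 2b/3, and the squared deviations sum to (b/3)² + (b/3)² + (2b/3)² = 2b²/3. The noncentrality parameter is λ = n × 2b²/3. The rejection probability is P(F′ > F crit), where F′ is noncentral F with 2 and 3n − 3 degrees of freedom.

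| n per arm | df | F crit | b | λ | P(reject) |
|---|---|---|---|---|---|
| 38 | 2, 111 | 3.078 | 0.2 | 38 × 0.0267 = 1.013 | 0.132 |
| 38 | 2, 111 | 3.078 | 0.3 | 38 × 0.06 = 2.28 | 0.247 |
| 38 | 2, 111 | 3.078 | 0.5 | 38 × 0.1667 = 6.333 | 0.596 |
| 30 | 2, 87 | 3.101 | 0.2 | 0.8 | 0.113 |
| 30 | 2, 87 | 3.101 | 0.3 | 1.8 | 0.201 |
| 30 | 2, 87 | 3.101 | 0.5 | 5.0 | 0.489 |

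With b = 0 the probability is 0.05.

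**Step 4: the same shift in the planned pairwise contrasts.** EA versus IVF has expected difference b, so it carries the whole shift. EA versus pEA has expected difference b − b = 0, so it is unaffected.

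**The case against.** **The limit is disclosed.** The Blinding section opens with it, the Highlights state it, the blinding assessment is confined to EA and pEA, and lack of blinding against the IVF arm is the first limitation listed. This stands: an attentive reader is not deceived. It does not make the two unqualified statements correct.

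**The overall test is valid.** If EA and pEA both differ from IVF, the three means do differ, and rejection is right. This also stands. The figures above are not false-positive rates of a faulty test. The harm arises only if the overall result, or EA versus IVF, is read as a blinded efficacy effect. The article does not say it will be read that way, and EA versus pEA is already planned. But that contrast is post hoc, and nothing says it governs the reading of the scales.

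**The stakes are modest.** The scales are secondary, the primary outcome is an ultrasound-confirmed gestational sac, and the pilot is exploratory. This limits the weight of the point without removing it.

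**A stronger reading is tempting.** Because "Egg retrieval, fertilization, and embryo transfer were determined by their fertility specialists", and gonadotrophin dose and stimulation duration are reported, a reader might infer that the specialists' blind must fail too and that these outcomes and the pregnancy rate are compromised. The article does not support that. It says the specialists are blinded and nowhere says they know the allocation. Acupuncture is given by other staff, and allocation runs through an independent third party by telephone. Disclosure by patients is a possible risk, not a demonstrated contradiction. Procedures to prevent it are operational detail that a condensed article may leave to the full protocol.

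**Conclusion.** The point holds for participant blinding and the self-rated scales. Two statements claim a blind that one third of the women (38 of 114) cannot have, in conflict with limits given elsewhere in the same article. For SAS, SDS, PSQI and FertiQoL, neither the overall test nor EA versus IVF can separate an effect of EA from expectation and attention, yet EA versus pEA, which can, is not the lead comparison.

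The illustrative size is a significant three-group result in about 13% to 60% of trials at 38 per arm (11% to 49% at 30) with no EA effect beyond sham. It rests wholly on assumed shifts of 0.2 to 0.5 SD, equal response in EA and pEA, and a successful blind between those two arms. The inconsistency in the wording needs no assumption.

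The point does not extend to the blinding of fertility specialists or to the primary outcome. It should be corrected, since it changes what can be concluded from the scales, but it does not threaten the trial as a whole.

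**What to change.** 1. In the Blinding section and in the Discussion paragraph on design strengths, say that participants are blinded in the EA and pEA arms only.
2. In the Statistical analysis section, make EA versus pEA the lead comparison for SAS, SDS, PSQI and FertiQoL, specified in advance rather than post hoc, with the three-group test as supportive.
3. Label EA versus IVF on these scales as open-label, and base no efficacy statement on it alone.

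The cost is wording only. Sample size, treatment, visits and data collection are unchanged, so the revision covers women already randomised. The downside is that the EA-versus-IVF result on the scales carries less weight.
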